##### Asthma control

Asthma control will be measured by the well-established “Asthma Control Test” (ACT), which is a reliable and valid tool to identify patients with poorly controlled asthma [32]. The ACT is a 5-item instrument assessing asthma symptoms, use of reliever medication, and the effect of asthma on daily functioning (e.g., “In the past 4 weeks, how much of the time did your asthma keep you from getting as much done at work, school or at home?”). The ACT’s potential score ranges from 5 (very poorly controlled) to 25 (completely controlled) with higher scores indicating better control. A score of 19 or less has been defined as a cut-off score suggesting poor control [32].

##### Asthma-related quality of life

The “Marks Asthma Quality of Life Questionnaire” (AQLQ-M) includes 20 items that can be divided into 4 domains and sub scores: (1) breathlessness, (2) mood disturbance, (3) social disruption, and (4) health concerns. Individual items are scored from 0 (“not at all”) to 4 (“very severely”). In total scoring the AQLQ-M, higher scores represent a greater impact of asthma on quality of life. Internal consistency has shown to be high (Cronbach’s alpha for the total score of 0.92) and test-retest reliability has been shown to be adequate [33].

##### Subjective employment prognosis

The “Brief Scale Measuring the Subjective Prognosis of Gainful Employment” (SPE-scale) consists of three items with the following contents: (1) the expectation of being able to work until reaching the statutory retirement age due to the current state of health, (2) the permanent (subjective) threat to earning capacity due to the current state of health, and (3) the current thought of applying for a pension. The internal consistency and predictive validity could be confirmed [34, 35].

**Table 2 Tab2:** Measures and survey times

Outcome	Measured by/Instrument	T0– screening	T1– rehabilitation start	T2– rehabilitation end	T3– 3-month follow-up
*Screening question*: Diagnosis “asthma” made by a physician, before the start of the COVID 19 pandemic in march 2020^1,2^	Self-developed	X			
*Screening question*: Employed for at least six months in an employment relationship subject to social insurance contributions or civil servant^1^	Self-developed	X			
*Screening question*: Working at least 15 h a week^1^	Self-developed	X			
Demographic information^3,4^	Self-developed	X	X	X	X
Asthma trigger	Self-developed		X	X	X
Sick days	Self-developed		X		X
Exacerbations	Partly adopted from “EPRA”^5^ -study [31]		X	X^9^	X
Information on treatment	Self-developed		X		X
Asthma self-management	Partly adopted from “EPRA”^5^-study [31]		X	X	X
Need for medical-occupational rehabilitation (MBOR)	Würzburger Screening [36]	X	X	X	Partly
Subjective prognosis of gainful employment	Brief Scale Measuring the Subjective Prognosis of Gainful Employment [34]		X	X	X
Information on occupation	Self-developed		X		X
Work satisfaction	Self-developed		X	X	X
Workability	First item from Work Ability Index [37]		X	X	X
Working conditions (related to asthma)	Determinants of Work-related Asthma Self-management Questionnaire [6]		X	X	X
Changes in working conditions	Self-developed				X
Asthma self-management at work (primary outcome T3)	Self-developed [6]		X	X	X
Behavioural intention regarding asthma self-management at work (primary outcome T2)	Self-developed		X	X	X
Workplace-related self-efficacy	Self-developed		X	X	X
Self-management-related knowledge (on “Asthma and Work”)	Self-developed		X	X	X
Job decision latitude	Copenhagen Psychosocial Questionnaire [38]		X	X	X
Social support at work	Copenhagen Psychosocial Questionnaire [38]		X	X	X
Asthma control	Asthma Control Test [32]	X	X	X	X
Quality of Life	Marks Asthma Quality of Life Questionnaire [33]		X	X	X
	Visual analog scale from European Quality of Life 5 Dimensions Questionnaire [39]		X	X	X
COVID-19	Self-developed/partly adopted from COVIDOM-study^6^ [40]		X	X^9^	X
Further health aspects^7^	Partly adopted from “EPRA”^5^-study [31]		X	X	X
Depressiveness	Patient Health Questionnaire-2 [41]		X	X	X
Anxiety	Generalized Anxiety Disorder Questionnaire-2 [41]		X	X	X
Body Mass Index^8^	Weight, height		X		
Lung function^8^	Forced expiratory volume in 1 s (FEV1), FEV1/vital capacity, total specific airway resistance, vital capacity, residual volume		X	X	
Exercise capacity^8^	6-minute walk test [42]		X	X	
Allergy^8^	Total immunoglobulin E (Ig E), specific Ig E-Screening (ImmunoCAP®)		X		
Asthmatic inflammation^8^	Fractional exhaled nitric oxide (FeNO), Eosinophils/µl		X		
Medication^9^	Asthma medication and changes		X	X	

^1^Inclusion criterion

^2^To ensure that asthma, not long/post COVID is the leading diagnosis

^3^Items vary slightly at different measurement time points

^4^Covariates of univariate analyses of covariance

^5^Effectiveness of Pneumological Rehabilitation in Bronchial Asthma

^6^Population-representative study of the sequelaes of COVID-19

^7^Includes physical activity, smoking behaviour, and doing relaxation procedures

^8^Assessed by a study nurse (with the help of a physician questionnaire)

^9^Assessed by a physician (with the help of a physician questionnaire)

### Data analysis plan

The primary statistical analysis will be based on the intention-to-treat (ITT) sample, that is, all participants as randomized. Since the ITT includes all participants for whom treatment was intended, data from individuals who, for example, did not ultimately receive the intervention or did not receive it completely (e.g., due to premature drop-out) are also included in the evaluation. Thus, the evaluation strategy based on the ITT principle is assumed to resemble outcomes that may be achieved in everyday life. Therefore, a secondary analysis based on the per-protocol collective (PP) will be performed. Here, all participants are excluded for whom the study treatment deviated from the study protocol (e.g., no participation in session 1 and/or 2). Since the PP only includes those participants who completed the study in compliance with the study protocol, the results may be biased in favour of the intervention. If the evaluation of the primary outcomes (see above) according to the ITT and PP principles provides similar results, confidence in the reliability of findings increases. If this is not the case, then possible reasons for the discrepancy between the two approaches will be discussed [43, 44].

The following describes the analyses in detail: Descriptive statistics, including means for continuous variables and proportions for categorical variables, will be used to summarize participant characteristics. We will determine the potential changes in primary and secondary outcomes (T1 to T2, T1 to T3) by pre-post comparisons within groups and test them for statistical significance using paired t-tests. Differences between groups (at T2 and T3) will be evaluated using univariate analyses of covariance (ANCOVAs). That is, membership in the intervention or control group will be used as the independent variable in each case, and the follow-up score of the primary outcome measures (behavioural intention, asthma self-management at work) and secondary outcome measures (self-efficacy, self-management-related knowledge, number of sick days, number of exacerbations, asthma control, asthma-related quality of life, and subjective employment prognosis) will be used as the dependent variable. Initially, only the corresponding baseline value of the primary outcome variable is included as a covariate to remove conditional bias [45, 46]. In a next step, the rehabilitation clinic [47], gender, age [48], and education [48] are additionally included as covariates. If the correlation between baseline and follow-up values is high (> 0.5), change scores are used as independent variables instead of follow-up values, as these then provide a more precise estimate [49]. For all models, the statistical model assumptions (linearity, homoscedasticity, normality of residuals) are tested. If the model assumptions are violated, appropriate analysis methods (e.g., robust regression, log transformation) are applied. In addition, to test whether comorbid COPD or long/post COVID disease affects the outcomes, sensitivity analyses will be performed excluding participants with COPD and/or long/post COVID symptoms. We will also conduct the analyses again without those who participated during the pre-test^2^, as at this point there may not yet be a routine regarding the training procedures and minor adjustments may still be made. Gender-stratified analyses are also conducted. Likewise, those with uncontrolled (ACT < 20 [32]) versus controlled asthma (ACT ≥ 20 [32]) and those with versus without a need for medical-occupational rehabilitation^3^ should additionally be analysed separately. Our primary analysis will be based on complete case analysis. In case the proportion of missing data exceeds 5% on a given variable, we will carry out sensitivity analysis employing multiple imputations.

Furthermore, the extent to which effects that may be observed are clinically relevant will be considered. In this context, the concept of “minimal clinically important difference” (MCID) is relevant. The MCID refers to the smallest change (i.e., improvement) that might be relevant to patients [50, 51]. Among other methods, the MCID can be estimated based on distribution. These include calculating MCID based on observed change, e.g., 1/2 standard deviation of change score [52]. This method has been recommended, particularly for smaller effects [52], and will therefore be used in the present study to assess whether potentially observed effects are clinically relevant.

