### Sample size

We assume that over a period of 11 months, we will be able to recruit approximately 300 individuals who meet the inclusion criteria (Bad Ems: *n* ≥ 100, Bad Reichenhall: *n* ≥ 200). With a drop-out rate of 40% by T3, we can assume a sample of 180 participants (90 per group) attending at all measurement time points (Bad Ems: *n* ≥ 60, Bad Reichenhall: *n* ≥ 120). With an intermediate effect size of Cohen’s d = 0.5 [24], an alpha level of 0.05, and a statistical power of 0.8, this sample size should be sufficient to detect significant differences and the sample size is comparable to or exceeds that of similar RCTs [25–28].

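### The switch to change scores above a correlation of 0.5 rests on a wrong rationale: against the planned baseline-adjusted ANCOVA it offers no meaningful gain in precision, and it loses precision if the baseline covariate is dropped

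*Protocol article*

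**What the plan says.** All of this stands in one paragraph of the Data analysis plan.

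- Method: "Differences between groups (at T2 and T3) will be evaluated using univariate analyses of covariance (ANCOVAs").
- Predictor: "membership in the intervention or control group will be used as the independent variable in each case".
- Outcome: the follow-up score of each primary and secondary measure "will be used as the dependent variable".
- Baseline adjustment: "Initially, only the corresponding baseline value of the primary outcome variable is included as a covariate to remove conditional bias". Clinic, gender, age and education are added in a second step.
- Switching rule, for a baseline/follow-up correlation above 0.5: "change scores are used as independent variables instead of follow-up values, as these then provide a more precise estimate".

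The paragraph does not say whether the baseline covariate stays in the model after the switch. The rule covers both primary outcomes, behavioural intention at T2 and asthma self-management at work at T3.

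**The concern.** A threshold of 0.5 is the familiar break-even point between analysing raw change and analysing the follow-up score with no use of baseline. This plan does not use an unadjusted follow-up analysis, because its first model already contains the baseline value. The gain in precision that justifies the switch has therefore already been obtained, and more, by the covariate.

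The clarity and efficiency of the primary analysis are at stake. Two analysts could follow the sentence in good faith, one keeping the baseline covariate and one dropping it, and report different estimates and standard errors for the same primary outcome. The second would give up precision on the strength of a reason that is not true for this plan.

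**Working it through.** **Inputs.** From the Data analysis plan: the threshold r > 0.5, and ANCOVA with baseline as covariate. From Sample size: "With an intermediate effect size of Cohen’s d = 0.5 [24], an alpha level of 0.05, and a statistical power of 0.8", with 300 recruited, 40% drop-out and 90 per group. Not in the document: the actual correlation, the SDs and the sidedness of the test. I assume r from 0.5 to 0.95, equal SDs at first, a two-sided test, and d expressed in follow-up SDs.

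**1. The plan's own figure.** 300 × 0.6 = 180, or 90 per group. For d = 0.5 at 80% power an unadjusted comparison needs 2 × (1.960 + 0.842)² / 0.5² ≈ 63 per group. Power at 90 per group is 0.918 (0.916 with the t distribution). So 180 reproduces and is sufficient, without relying on any baseline adjustment.

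**2. Where 0.5 comes from.** Variance of the group difference, in units of the unadjusted follow-up analysis, equal SDs:

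- follow-up score, unadjusted: 1
- raw change score: 2(1 − r)
- ANCOVA with baseline: 1 − r²

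2(1 − r) < 1 exactly when r > 0.5. That is change against *unadjusted* follow-up.

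**3. The comparison that matters here.** Change against ANCOVA: 2(1 − r)/(1 − r²) = 2/(1 + r), which is above 1 for every r below 1. The simulated column uses 20,000 trials per value of r, 90 per arm.

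| r | Change | ANCOVA | Ratio | Simulated ratio |
|---|---|---|---|---|
| 0.51 | 0.98 | 0.740 | 1.32 | 1.31 |
| 0.6 | 0.80 | 0.640 | 1.25 | 1.24 |
| 0.7 | 0.60 | 0.510 | 1.18 | 1.18 |
| 0.8 | 0.40 | 0.360 | 1.11 | 1.10 |
| 0.9 | 0.20 | 0.190 | 1.05 | 1.05 |

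At r = 0.51, 180 participants analysed by raw change carry the information of 180/1.3245 ≈ 136 analysed by ANCOVA.

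**4. Unequal SDs.** With k = baseline SD / follow-up SD, the ratio is 1 + (k − r)²/(1 − r²). It is never below 1, and equals 1 only when k = r. For k of 0.7, 1 and 1.3 and r of 0.5, 0.6 and 0.8 it runs from 1.02 to 1.85. The cut-off itself also moves: change beats unadjusted follow-up when r > k/2, so 0.5 is right only for equal SDs.

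**5. Baseline kept, change as outcome.** If Y = a + τG + bX + e, then Y − X = a + τG + (b − 1)X + e. Only the slope on X changes; τ, the residuals and the standard error do not. In the simulations the two estimates differed by less than 1e-15. Adding clinic, gender, age and education alters nothing here, provided X stays in.

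**6. Chance imbalance if baseline is dropped.** Raw change subtracts the whole baseline difference, whereas ANCOVA subtracts r times it (equal SDs). The two estimates differ by (1 − r) × imbalance. One standard error of imbalance at 90 per arm is √(2/90) ≈ 0.149 SD. At r = 0.51 this gives 0.49 × 0.149 ≈ 0.073 SD, about 15% of d = 0.5.

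**7. Power at 90 per arm, raw change against ANCOVA.** At d = 0.5: 0.923 against 0.974 (r = 0.51) and 0.963 against 0.987 (r = 0.6). At a smaller d of 0.35, which is my assumption: 0.660 against 0.779 (r = 0.51), 0.747 against 0.835 (r = 0.6) and 0.858 against 0.908 (r = 0.7).

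**The case against.** The strongest reply is that the text swaps only the follow-up value for the change score. It nowhere removes the baseline covariate or abandons ANCOVA. Read that way, the sentence is redundant and harmless: no estimate, standard error or conclusion changes. This stands, and it makes all the figures on lost precision and over-correction conditional on a step that the text leaves open but does not state.

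A reader might infer several stronger things, which the document does not support:

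- *That the plan specifies an invalid model with change as a predictor.* The same paragraph makes group the predictor and the follow-up score the outcome. Change takes the place of the follow-up score, so it belongs in the outcome position. The wording is most likely a slip.
- *That the trial loses a quarter of its information.* That is the equal-SD figure just above the threshold with baseline dropped. It shrinks to 5% in variance at r = 0.9, and no correlation is given.
- *That the trial becomes underpowered for its stated effect.* Sample size never counted on the efficiency of ANCOVA, and power at d = 0.5 stays above 0.8 either way.
- *That this is a results-driven choice of primary analysis.* The threshold is fixed in advance and does not depend on the treatment effect, and a pooled correlation needs no group labels. Two outcomes could still be handled differently for no benefit, but this is minor.
- *That the raw change estimator is biased.* Under randomisation it is unbiased overall; the over-correction concerns the imbalance actually observed.

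The absence of any gain is a large-sample result. With 180 analysed, estimating the slope costs about 0.6% of variance, so raw change could win trivially at r near 0.99 (simulated ratio 0.997). The source cited for the rule cannot be seen, so what it recommends is not judged here. None of this rescues the stated reason.

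**Conclusion.** The point holds in limited form. The reason given for the switching rule is wrong for this plan, because it compares change with an analysis that the plan does not use. On one reading the rule has no effect. On the other it raises variance by 2/(1 + r) under equal SDs, from about 32% just above the threshold to 11% at r = 0.8, and brings back dependence on chance baseline imbalance that the covariate was included to remove. Which reading applies cannot be settled from the text. The size of any loss rests on an unknown correlation and SD ratio. The sample size is not affected. This is a faulty rationale and an ambiguous instruction for the primary outcomes, to be corrected before analysis; it does not threaten the design.

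**What to change.** Delete the switching sentence. State that each continuous outcome is analysed by ANCOVA with the follow-up score as dependent variable and its own T1 value as covariate, whatever the correlation. If the investigators prefer to present change as the outcome, name it as the dependent variable and say that the T1 covariate stays in the model; the group estimate and standard error will then be the same. The planned within-group paired t-tests are outside this point and need not be removed. The cost is one sentence, with no effect on sample size, data collection or the other planned analyses.

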**Discussion:**

Improving asthma self-management at work could increase the work ability and social participation of employees with asthma. This could reduce costs, e.g. in terms of asthma-related sick leave.

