We hypothesise that the behavioural intention related to the implementation of appropriate asthma self-management will improve at the end of the rehabilitation program (T2). As mentioned above, the behavioural intention is considered a key determinant of successful asthma self-management at work [15, 20]. Then, after 3 months and the possible return to work (T3), actual asthma self-management at work should have improved due to prior proactive initiation of changes of relevant individual working conditions. Thus, behavioural intention will be used as primary outcome at T2 while asthma self-management will serve as primary outcome at T3. Self-management-related knowledge and self-efficacy along with other factors (see below) will represent the secondary outcomes. The potential improvement in asthma self-management at work and related improvement in asthma control, asthma-related quality of life, and the subjective employment prognosis (see above) [6, 7] could then reduce the number of exacerbations and sick days (and also related costs). Therefore, we will also examine asthma control, asthma-related quality of life, the subjective employment prognosis, and the number of exacerbations and sick days as secondary outcomes.

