##### Number of asthma-related sick days

To examine the number of days of incapacity, we will ask the following question: “How many working days within the last three months (T3: since the end of rehabilitation) were you not able to work due to your asthma and… a)…called in sick (without a sick note)? b)…got a sick note from your physician?”

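### For sick days, the example fallbacks (robust regression, log transformation) can replace the difference in mean days with another quantity and pull the estimate toward zero

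*Protocol article*

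**What the plan says.** In the protocol article, the section on the number of asthma-related sick days defines the outcome by a self-report item: "How many working days within the last three months (T3: since the end of rehabilitation) were you not able to work". Table 2 places it at T1 and T3.

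The Data analysis plan lists it among the "secondary outcome measures (self-efficacy, self-management-related knowledge, number of sick days, number of exacerbations" and others, each used as the dependent variable of an ANCOVA. It then states: "For all models, the statistical model assumptions (linearity, homoscedasticity, normality of residuals) are tested". The next sentence gives the remedy: "If the model assumptions are violated, appropriate analysis methods (e.g., robust regression, log transformation) are applied". No estimator is named for robust regression, and sick days get no method of their own.

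The reason for measuring sick days is given in the Background, where better self-management "could then reduce the number of exacerbations and sick days (and also related costs") is expected, and in the abstract: "This could reduce costs, e.g. in terms of asthma-related sick leave".

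**The concern.** ANCOVA on the T3 value estimates a difference in mean days between arms. That is also the quantity on which a saving in sick leave or cost depends, because cost follows total days.

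Sick days over about three months cannot fall below zero. Many participants may have none and a few may have long absences. Residuals from such data are skewed, so the normality check will very likely fail and the fallback will then shape the sick-day analysis.

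M-type robust regression limits or removes the influence of large residuals. For bounded questionnaire scores this changes little. For sick days the large residuals are the long absences, and with many zeros the estimated residual scale is small, so even moderate absences are down-weighted. The coefficient then describes the bulk of the sample, not mean days. A real reduction in days could be reported as small or absent.

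**Working it through.** **Inputs from the article.** The Sample size section gives 300 recruited and 40% drop-out: 300 × (1 − 0.40) = 180, or 90 per arm. This reproduces the stated figure and serves here only as the simulation size.

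**Inputs assumed.** The article gives no mean, share of zeros or share of days from long absences, so a range is used. All simulations cap days at 63 and adjust for T1 days.

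**Step 1: negative-binomial counts.** Control mean 4 days, intervention mean 2, true difference −2.0 days, 300 simulated trials per setting. With dispersion k, the control share of zeros is (k / (k + 4))^k:
- k = 0.15: (0.15/4.15)^0.15 = 0.61
- k = 0.25: (0.25/4.25)^0.25 = 0.49
- k = 0.5: (0.5/4.5)^0.5 = 0.33
- k = 1.0: 1/5 = 0.20

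A Shapiro test rejected residual normality in 100% of trials at every k. Mean estimates:

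| k | ANCOVA (days) | Huber (days) | Tukey biweight (days) | Huber ÷ −2.0 | Ratio from log(1+days); true ratio of means 0.50 |
|---|---|---|---|---|---|
| 0.15 | −1.86 | −0.18 | −0.01 | 9% | 0.81 |
| 0.25 | −2.03 | −0.60 | −0.12 | 30% | 0.75 |
| 0.5 | −1.97 | −1.05 | −0.53 | 53% | 0.70 |
| 1.0 | −1.99 | −1.39 | −1.10 | 70% | 0.65 |

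In a separate run of 400 trials at the first three values of k, a Poisson log-link model with robust standard errors recovered a ratio of about 0.50. Its power was 0.55, 0.69 and 0.92, against 0.31, 0.41 and 0.81 for Huber. A plain log cannot be used at all for participants with 0 days.

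**Step 2: where the saving lies.** Mixture of zero, short and long absences, 400 trials per scenario, T1 days drawn independently of T3. Mean days = P(short) × mean short + P(long) × mean long. In the first row, control is 0.30 × 3 + 0.10 × 25 = 3.40 and intervention 0.30 × 3 + 0.05 × 25 = 2.15, a difference of −1.25. The true differences below are simulated with the cap.

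| Scenario (control zeros) | True (days) | ANCOVA | Huber | Tukey biweight | Huber ÷ true |
|---|---|---|---|---|---|
| Long absences halved, slightly more zeros (60%) | −1.25 | −1.21 | −0.20 | −0.02 | 16% |
| Half of long absences become short (60%) | −1.07 | −1.08 | −0.06 | +0.07 | 6% |
| Long absences shortened from 25 to 15 days (60%) | −0.98 | −0.92 | 0.00 | 0.00 | 0% |
| Long absences halved, more zeros (75%) | −1.03 | −1.10 | −0.01 | 0.00 | 1% |
| Half of long absences become short (40%) | −1.05 | −1.04 | −0.19 | +0.05 | 18% |
| All absences 30% shorter (30%) | −1.66 | −1.62 | −0.98 | −0.89 | 59% |
| Zeros rise from 40% to 60% | −1.44 | −1.48 | −0.96 | −0.87 | 67% |
| Few zeros, few long absences, short ones shortened (10%) | −1.73 | −1.72 | −1.91 | −1.88 | 110% |

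In the control arm, absences of 10 days or more carried between 21% (last row) and 78% (fourth row) of all days. ANCOVA is right on average in every row but imprecise: its sampling SD is about 0.6 to 1.2 days.

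**The case against.** The strongest reply is that the article does not fix M-estimation for sick days. Robust regression and log transformation are examples under the heading of appropriate methods, so a count model or bootstrap is already allowed, and the choice for each outcome may stand in an analysis plan not shown. This stands in part: the article does not commit the analyst to a poor method. But the rule covers all models, and for this outcome both named examples, in their usual meaning, leave mean days. The point concerns what is stated, not missing detail.

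Second, robust regression may mean ordinary least squares with robust standard errors. Homoscedasticity is among the assumptions checked, so this is a possible reading, and under it the mean difference is untouched. The text does not settle the matter, and in the most zero-heavy setting of step 1 it separates about −1.9 from about −0.2 days.

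Third, a reader might infer that the fallback generally reports a real saving as near zero, or even reverses its sign. The documents do not support that. They give no sick-day distribution and do not say that a few long absences carry most lost days. Huber keeps about 60% or more of the saving when it is spread over many participants, and all of it when zeros and long absences are few. A clear Huber sign change was seen only in a constructed case where short absences rise sharply (long from 10% to 5%, short from 30% to 45%: mean −0.7 days, Huber +0.2).

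Fourth, the plan also has within-group paired t-tests, which show mean change in days per arm. True, but they do not compare the arms. Nor does the article describe a cost analysis; it says only that costs could fall.

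**Conclusion.** The point holds in conditional form. The normality check will very likely fail for sick days. If the analyst then uses M-estimation, the estimate is no longer the difference in mean days. Under the assumed negative-binomial counts, Huber retains roughly 10% of a 2.0-day saving (over 60% zeros) to 70% (about 20% zeros). Where the saving lies in a few long absences, it retains 0% to 18%. Analysis of log(1+days) does not yield a ratio of mean days either.

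These sizes rest on assumed distributions and on reading robust regression as M-estimation; with robust standard errors only, the defect disappears. A failure to detect a saving would not be due to the fallback alone, because ANCOVA itself has an SD of about one day against savings of about one day in most of the scenarios.

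Sick days are a secondary outcome. The primary outcomes, their conclusions and the sample size are unaffected.

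**What to change.** In the Data analysis plan, exempt sick days from the generic fallback and name from the outset a method that keeps mean days. Either of these would do:
- a log-link count model (negative binomial, or Poisson-type with robust standard errors), adjusted for T1 sick days, for example as log(1+days), giving a ratio of mean days;
- the planned ANCOVA with sandwich or bootstrap errors.

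In both cases report the arm difference in mean days with a bootstrap interval. If robust regression was meant as robust standard errors, say so.

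The cost is one or two sentences and no new data. A ratio of means has to be explained to readers, and intervals will stay wide if few participants have long absences.

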### Intervention

Both groups will receive a 3-week rehabilitation program that meets the structural requirements of German healthcare insurance providers (standards for personnel, space, and medical-technical equipment) [29, 30]. The rehabilitation program includes, among other things, different non-drug therapy components such as physical training, respiratory physiotherapy, comprehensive patient education, and psychosocial counselling [31]. In addition, patients will receive a routine check-up and if necessary, the current asthma medication will be adapted according to the current guidelines (any changes to medication will be documented).

The participants of the intervention group will additionally receive the module “Asthma and Work” in a workshop with preferably about five participants each. This education module spans across 2 × 50 minutes. It offers in the first part (module A) a theoretical introduction to the topic/knowledge transfer in the form of lectures (e.g., “What is asthma self-management in general and in the workplace?” and “What does ‘job crafting’ mean?“) as well as individual and plenary exercises (peer support). In the second part (module B), the focus is on practical exercises, especially in the form of communication training and role plays (e.g., “How do I communicate specific change requests regarding my working conditions?”).

The control group, by contrast, will receive an education module addressing “Eating behaviour”. We chose this topic because eating behaviour is not part of asthma self-management behaviour. In addition to general topics of healthy nutrition (“What does a healthy diet look like? And why is a healthy diet important?”), this educational module focuses on the psychological aspects of eating (conscious and unconscious processes: Why do we eat, when and how? And how can we improve our eating behaviour?). This content is provided through lectures and exercises in individual and group work. It will have the same temporal scope (2 × 50 min) as the intervention module and will also take place in small groups and preferably in the same week of the pulmonary rehabilitation program.

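### Three subgroup factors are to be analysed stratum by stratum with no test of whether the module's effect differs between strata

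*Protocol article*

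**What the plan says.** All of the following is in the Data analysis plan section of the Protocol article unless noted.

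- **Subgroups.** "Gender-stratified analyses are also conducted". Uncontrolled versus controlled asthma (ACT cut at 20), and patients with versus without a need for medical-occupational rehabilitation, are likewise to be analysed separately. The article contains no interaction term or test of heterogeneity.
- **Within-arm change.** Change from T1 to T2 and from T1 to T3 in primary and secondary outcomes is to be assessed "by pre-post comparisons within groups and test them for statistical significance using paired t-tests".
- **Between-arm comparison.** The next sentence plans ANCOVAs at T2 and T3 with group as the independent variable, for every primary and secondary outcome. The baseline value is the first covariate.
- **Background care (Intervention section).** "Both groups will receive a 3-week rehabilitation program".
- **Planning values (Sample size section).** "With an intermediate effect size of Cohen’s d = 0.5", "an alpha level of 0.05, and a statistical power of 0.8", and 90 participants per group expected with data at all time points.

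**The concern.** A subgroup analysis adds one question to the overall result: does the effect of the module differ between, say, men and women? Two separate analyses give two p-values, each answering whether there is an effect in that stratum. Neither tests the difference. Each stratum has only part of the sample, so one p-value can easily fall below 0.05 and the other above it when the effects are the same. A report on those terms could suggest that the module suits one group of patients and not another, and so influence who is offered it.

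The paired t-tests raise a smaller issue of the same kind. Change within an arm combines the rehabilitation programme, any regression to the mean and, in the intervention arm, the module. A significant change in one arm beside a non-significant change in the other is not evidence about the module.

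**Working it through.** **1. The plan's own figure.** 300 × (1 − 0.40) = 180, or 90 per arm. For d = 0.5 and two-sided alpha 0.05 (sidedness is not stated; two-sided is assumed), a two-sample t-test needs 64 per arm for 80% power. With 90 per arm the power is 0.916. The statement that the sample is sufficient is confirmed for the overall comparison. The sample size is not in question here.

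**2. Separate analyses when the effect is the same in both strata.** Inputs: d = 0.5 in each stratum, 90 per arm in total, alpha 0.05 two-sided, two-sample t-test. Stratum shares are assumed. With powers p1 and p2 in two independent strata, the chance that exactly one is significant is p1(1 − p2) + p2(1 − p1).

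| Assumed split | n per arm in each stratum | p1 | p2 | Exactly one significant |
|---|---|---|---|---|
| 50/50 | 45 and 45 | 0.650 | 0.650 | 2 × 0.650 × 0.350 = 0.455 |
| 70/30 | 63 and 27 | 0.795 | 0.438 | 0.795 × 0.562 + 0.438 × 0.205 = 0.537 |
| 80/20 | 72 and 18 | 0.846 | 0.308 | 0.846 × 0.692 + 0.308 × 0.154 = 0.633 |

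A normal approximation gives 0.449, 0.529 and 0.624. If the module has no effect in either stratum, the figure is 2 × 0.05 × 0.95 = 0.095. The calculation ignores any precision gained from baseline adjustment. Such a gain would raise power in each stratum and lower the figure for an even split.

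**3. The interaction test instead.** The standard error of the difference between the two stratum effects, in SD units, is √(2/n1 + 2/n2). Power below is by normal approximation for a true difference in effects of 0.5 SD.

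| Assumed split | SE | Power | Difference needed for 80% power |
|---|---|---|---|
| 50/50 | √(2/45 + 2/45) = 0.298 | 0.39 | 0.84 SD |
| 70/30 | √(2/63 + 2/27) = 0.325 | 0.34 | 0.91 SD |
| 80/20 | √(2/72 + 2/18) = 0.373 | 0.27 | 1.04 SD |

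For comparison, the SE of the overall effect is √(2/90) = 0.149. When the effects are equal, the interaction test gives a false signal in 5% of trials per factor, against the 45% to 63% discordance in step 2.

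**4. Paired t-tests with no module effect.** Assume the same true change in both arms, expressed in SDs of the change score, with n = 90 per arm and 89 df. If p is the power of one paired test, the chance that only the intervention arm is significant is p(1 − p).

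| Assumed standardised change | p | Intervention arm only |
|---|---|---|
| 0.1 | 0.155 | 13% |
| 0.2 | 0.467 | 25% |
| 0.3 | 0.804 | 16% |
| 0.4 | 0.964 | 3.5% |
| 0.5 | 0.997 | 0.3% |

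The documents give no expected change, so the range matters more than any single row. These are probabilities of a pattern of p-values, not of a wrong trial conclusion. The 90 per arm is the number expected with data at all time points; the number available at T2 may be larger.

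**The case against.** **Effectiveness is tested directly.** A reader might infer from the paired t-tests that the module's effectiveness will be judged by comparing within-arm p-values. The article does not support that reading. The sentence after the paired tests plans the between-group ANCOVA for every primary and secondary outcome, and the Abstract also names ANCOVA as the method. This objection stands in full against any claim that the arm contrast goes untested. What remains is narrower. The within-arm tests are described as significance tests and nothing marks them as descriptive. The T2 hypothesis in the Background section speaks of improvement without naming a comparator.

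**No differential claim is announced.** A reader might equally infer that effect modification will be declared when one stratum is significant and the other is not. The article does not say so. The subgroup analyses are presented as additional, with no hypothesis of differential effect and no decision rule. This limits the weight of the point but does not remove it, because comparing the strata is the natural use of paired subgroup results and nothing else is offered for it.

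**An unseen analysis plan could add the interaction.** That is possible, and silence alone would not be a finding. Here, however, the article introduces its description as detailed and fixes a method, namely separate analyses. The point concerns the method stated.

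**Interaction tests would be weak.** This is correct, as step 3 of the working shows. Low power is a reason to call the analyses exploratory and show intervals. Separate p-values carry the same imprecision without showing it.

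**Conclusion.** The point holds for the subgroup analyses. As written, the plan examines three factors by a method that does not test for a difference in effect. Under the trial's own planning effect, shared equally by both strata, a discordant pair of p-values would arise in roughly 45% to 63% of trials per factor. That range rests on 90 analysable participants per arm, two-sided testing at 0.05, and assumed splits from 50/50 to 80/20. The consequence is a risk to secondary, exploratory conclusions. The primary comparison and the sample size are unaffected.

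For the paired t-tests only a minor reporting point holds. They cannot isolate the module because both arms are in rehabilitation, and with no module effect they could show a change in the intervention arm only in 0.3% to 25% of trials over assumed changes of 0.1 to 0.5. The ANCOVA already supplies the proper test of effectiveness.

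**What to change.** **Subgroups.** For gender, ACT group and need for medical-occupational rehabilitation, add an arm-by-subgroup interaction term to the ANCOVA, one factor at a time. Define ACT group and rehabilitation need by their T1 values: Table 2 shows both measured repeatedly, and ACT is itself an outcome. Report the module's effect in each stratum with a confidence interval, base any statement about differential effect on the interaction alone, and label these analyses exploratory.

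**Within-arm change.** Report mean change per arm with confidence intervals in place of the step to "test them for statistical significance using paired t-tests", and state that effectiveness rests on the between-group ANCOVA alone.

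**Cost.** A few sentences and three additional model terms, with no change to data collection, conduct or sample size. The downside is that differential claims become harder to make, since even an evenly split factor would need a difference of about 0.84 SD for 80% power.
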